#### Secondary clinical outcomes

The main secondary outcome is the PC-QOL score. Other outcomes are 1) the time to next exacerbation; 2) requirement for hospitalization; 3) duration of exacerbation (persistence of symptoms till return to baseline state); and 4) FEV_1_ % predicted.

#### Secondary laboratory outcomes

Serum markers (CRP, SAA, IL-6, IL-10, IP-10) and data on viruses and respiratory bacterial pathogens, including their antibiotic susceptibility to penicillin and azithromycin.

### Sample size

We plan to enroll 170 children (85 per arm), providing 90% power (α = 0.05, 1-sided) with 20% non-inferiority margin to detect 80% resolution rate by day 21. The margin selected is relatively large in statistical terms, but the physicians considered it clinically appropriate. As the primary outcome will be obtained in all enrolled children, retention fraction has not been factored in for the intention-to-treat analysis.

The main secondary outcome (secondary aim 1) is PC-QOL. Based on a non-inferiority limit of 0.9 (minimum important difference [57]) and standard deviation of 0.9, our sample size provides a power of 99.9% (α = 0.05, one-sided 95% CI) for data from at least 136 children (assuming at least 80% retention of children enrolled). For secondary aim 2 (see list under ‘Aims of the study’), we will be examining eight main factors, and thus a sample size of 136 exceeds the recommended minimum (n = 10 per factor) [65]. The eight factors are: smoking, age, underlying etiology, detection of virus (any versus none, then single versus multiple viruses), presence of azithromycin resistance, and levels of various blood markers (IL-6, IL-10, IP-10).

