### Intervention and follow-up

A double-dummy design is planned. If eligibility is fulfilled, and after informed consent has been obtained, the child will be randomized to one of two arms. At the start of the exacerbation, the child will receive orally: 1) azithromycin with placebo amoxycillin-clavulanate or 2) amoxycillin-clavulanate with placebo azithromycin. The azithromycin dose is 5 mg/kg/day (to a maximum of 200 mg daily, and for amoxycillin-clavulanate it is 22.5 mg/kg/dose twice daily (maximum 900 mg/dose). Equivalent volumes of placebo will be given for both trial medications. All treatments will continue for 21 days.

An exacerbation is defined as an increase in sputum volume or purulence, or change in cough (>20% increase in cough score [46] or type (dry to wet) [47]) for more than 3 days. We validated this definition in our prospective study, and found that the kappa values (between clinicians) of these symptoms and signs were excellent (>0.75) [48]. Daily diaries will also be collected during exacerbations until the scores for 2 or more days reflect the child’s baseline state, which for each child will be established at enrolment, prior to any exacerbations. This assessment consists of a combination of symptoms (daily cough (yes/no), cough quality (wet/dry/none), cough score [46] averaged over two consecutive days) and signs (sputum color (if any present) using a color chart card (BronkoTest Ltd, London, UK), and crackles on chest auscultation). Children will be reviewed on days 14 and 21, and at resolution of the exacerbation. The exacerbation is considered resolved when symptoms and signs are the same as the baseline state. Post-exacerbation, the children will be followed up and evaluated clinically every 3 months for a period of 18 months or until their next exacerbation (whichever is sooner). The time to next exacerbation will be determined by duration of days from the resolution of the current exacerbation to the beginning of the next exacerbation.

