### Randomization, allocation, and blinding

Upon enrolment, the child will be assigned to the next unique number on the appropriate stratified list. The allocation will be performed by the trial pharmacist at the Royal Children’s Hospital (Brisbane, Australia). Randomization is stratified by site (Brisbane, Darwin, Melbourne, Perth, Sydney, Auckland), age (≤5 or >5 years) and underlying etiology (idiopathic/post-pneumonia or all other causes). The randomization sequence is computer-generated and uses permuted blocks. The allocation sequence will be concealed at all times throughout the study. The computer-generated allocation sequence was prepared by a statistician external to the study team.

The specially manufactured placebo medications (Institute of Drug Technology Australia Ltd, Melbourne, Victoria, Australia), have a similar taste and color to their respective antibiotics. Both active medications (azithromycin and amoxycillin-clavulanate) will be repackaged and relabeled so that both antibiotics and their respective placebos are provided in identical opaque bottles. For all trial medications, equal volumes of water are added using a syringe and needle by punching the seal. Adherence will be assessed by parent report and return of empty bottles.

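### Children are allocated while stable and treated only if they later exacerbate, so the primary outcome cannot be obtained in every enrolled child, and the rule for the untreated is missing or biased towards non-inferiority

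*Protocol article*

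**What the plan says.** - **Timing of allocation** (Randomization, allocation, and blinding): "Upon enrolment, the child will be assigned to the next unique number on the appropriate stratified list".
- **State at allocation** (Intervention and follow-up): each child is compared with a baseline state "which for each child will be established at enrolment, prior to any exacerbations". Aims of the study also describes children as clinically stable at enrolment.
- **Timing of treatment** (Intervention and follow-up): "At the start of the exacerbation, the child will receive orally" one of the two double-dummy combinations. Under Recruitment, the interval before that is covered by monthly contact and 3-monthly review, and onset is reported by the parent. No maximum wait is given.
- **Primary outcome** (Outcome measures): resolution by day 21 of treatment, with withdrawals and children given additional antibiotics counted as non-resolved.
- **Analysis** (Statistical analysis and reporting): children are analysed as allocated, and drop-outs before the end point count as non-resolved.
- **Size** (Sample size): the target is 170, split equally between the arms, "providing 90% power (α = 0.05, 1-sided) with 20% non-inferiority margin to detect 80% resolution rate by day 21". The reason for making no allowance is "As the primary outcome will be obtained in all enrolled children, retention fraction has not been factored in for the intention-to-treat analysis". For the PC-QOL score the next paragraph gives power "for data from at least 136 children (assuming at least 80% retention of children enrolled").

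**The concern.** The primary outcome describes an exacerbation under treatment. Allocation comes before that exacerbation, by an unlimited wait, so some allocated children may never have the event that the outcome measures. The only reason given for making no attrition allowance is therefore not true of this design.

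The larger issue is the denominator. Counting failures as non-resolved is a familiar conservative choice in a superiority trial. In a non-inferiority trial, failures that are unrelated to treatment and equal in both arms shrink the observed difference, which favours the trial's own hypothesis. The margin and the 80% rate are both stated for resolution by day 21 of treatment, so they belong to treated children and not to a mixture of treated and untreated.

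**Working it through.** **Inputs.** From Sample size: 85 per arm, one-sided alpha 0.05, power 90%, margin 20 points (read as absolute), 80% resolution (taken for both arms). The share *f* of randomised children who never start study drug is not in the article. I use 5% to 30% as an assumed range.

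**1. The plan's own figure.** With unpooled variance, n per arm = 2(0.8)(0.2)(z_alpha + z_power)² / 0.2².
- One-sided 0.05: 0.32 × (1.645 + 1.282)² / 0.04 = 68.5, so 69 per arm (138 in total).
- One-sided 0.025: 0.32 × (1.960 + 1.282)² / 0.04 = 84.06, so 85 per arm (170 in total).

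The stated 85 is not reproduced at the written alpha. It is reproduced exactly at one-sided 0.025, with no allowance for loss. That mismatch is a separate point. It matters here only because it decides how much slack 170 contains.

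**2. Untreated children excluded.** Power = Φ(0.2 / √(0.32 / n) − z_alpha), with n = 85(1 − f) per arm. For n = 85: 0.2 / 0.0614 = 3.260, giving Φ(3.260 − 1.645) = 94.7% and Φ(3.260 − 1.960) = 90.3%.

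**3. Untreated children scored non-resolved.** Take a true deficit exactly at the margin among treated children (80% against 60%). The observed rates are 0.8(1 − f) and 0.6(1 − f), and the observed deficit is 0.2(1 − f). Type I error = Φ((0.2 − 0.2(1 − f)) / SE − z_alpha), with 85 per arm.
- f = 10%: rates 0.72 and 0.54; SE = √((0.2016 + 0.2484) / 85) = 0.0728; Φ(0.02 / 0.0728 − 1.645) = Φ(−1.370) = 8.5%.
- f = 20%: rates 0.64 and 0.48; SE = √((0.2304 + 0.2496) / 85) = 0.0751; Φ(0.04 / 0.0751 − 1.645) = Φ(−1.113) = 13.3%.

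| Untreated share (assumed) | Treated of 170 | 20-point deficit appears as | Type I error, nominal 5% | Type I error, nominal 2.5% | Power if excluded, one-sided 0.05 | Power if excluded, one-sided 0.025 |
|---|---|---|---|---|---|---|
| 0% | 170 | 20 | 5.0% | 2.5% | 94.7% | 90.3% |
| 5% | about 162 | 19 | 6.6% | 3.4% | 93.7% | 88.8% |
| 10% | 153 | 18 | 8.5% | 4.6% | 92.6% | 87.1% |
| 20% | 136 | 16 | 13.3% | 7.7% | 89.8% | 83.0% |
| 30% | 119 | 14 | 19.6% | 12.1% | 86.0% | 77.9% |

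The type I columns apply when untreated children are scored non-resolved, and the power columns when they are excluded. Scoring them non-resolved also costs power: at one-sided 0.05 it is 89.6% at f = 10% and 85.8% at f = 20%. With exclusion, 90% power at one-sided 0.05 survives a loss of up to 1 − 69/85 = 18.8%.

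**4. Is a non-zero share plausible?** Eligibility requires more than two exacerbations in 18 months, that is, at least three, or 2 per year. If that rate continued and followed a Poisson law (an assumption), exp(−3) = 5% would have none in 18 months and exp(−2) = 14% none in 12 months. The article sets neither window as a limit on the wait.

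**The case against.** Four arguments on the other side carry weight.

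- **Power does not collapse at the written alpha.** A reader might infer that 170 children cannot deliver 90% power, citing 83% with 20% loss excluded, or 77.5% with that loss scored non-resolved. Both figures need one-sided 0.025, which the article does not state. At the stated one-sided 0.05, 136 treated children still give 89.8%. This stands.
- **The 80% retention figure is not a direct contradiction.** It was given for PC-QOL, and the resulting 136 is used again for the predictor analysis. Both need observed data, whereas a binary outcome that counts withdrawals as failures can be scored without them. The figure shows that losses are expected, but it does not estimate how many children never exacerbate. This stands too.
- **The article does not say that never-treated children are non-resolved.** The listed exits concern deterioration during treatment and intolerance of study drug, and the outcome is worded around treated exacerbations. A treated-only denominator is therefore a fair reading, and a full protocol or analysis plan may define it. The dilution figures are thus conditional on the other reading. That reading remains open, because children are to be analysed as allocated and the drop-out rule is not limited to those who started treatment.
- **A per-protocol analysis is planned** and might drop untreated children, but it is secondary.

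None of this rescues the sentence itself. It is a positive statement about all enrolled children, and the missing allowance rests on it.

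**Conclusion.** The point holds for the false premise and the unsettled denominator. Allocation at enrolment and treatment at a later exacerbation cannot yield a day-21 status for every enrolled child. There is no rule for a child who stays in follow-up without exacerbating. The drop-out rule, if applied before treatment starts, would raise one-sided type I error from 5% to about 8.5% with 10% untreated and about 13% with 20%. These sizes rest on an assumed untreated share, equal in both arms, and on 80% resolution in the comparator arm.

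The point does not extend to a failed sample size. At one-sided 0.05, power is 94.7%, 92.6% and 89.8% for 170, 153 and 136 treated children. Only if one-sided 0.025 was intended does it fall from 90.3% to about 87% and 83%. Nor does it follow that randomisation must move to exacerbation onset. Randomisation had already begun, some children may be unable to attend at onset, and a treated-only set deals with the bias without a change of procedure.

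**What to change.** 1. Define the primary analysis set as all randomised children who start study drug for an exacerbation, analysed as allocated. Allocation is concealed and double-blind, and no study drug is taken before onset, so starting treatment should not depend on arm.
2. Limit the rule that a drop-out is non-resolved to children who leave after starting treatment.
3. Delete the sentence that the outcome will be obtained in all enrolled children. State power for the number expected to be treated, at the alpha intended.
4. Report by arm how many randomised children never started treatment, and why. This checks the assumption in item 1.

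The cost is wording in Sample size and in Statistical analysis and reporting, with no change to allocation or data collection. If the sponsor prefers to keep 170 treated children, enrolment becomes 170 / (1 − f): 179 at 5%, 189 at 10% and 213 at 20% untreated.

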**Methods:**

This will be a multicenter, randomized, double-blind, double-dummy, placebo-controlled, parallel group trial involving six Australian and New Zealand centers. In total, 170 eligible children will be stratified by site and bronchiectasis etiology, and randomized (allocation concealed) to receive: 1) azithromycin (5 mg/kg daily) with placebo amoxycillin-clavulanate or 2) amoxycillin-clavulanate (22.5 mg/kg twice daily) with placebo azithromycin for 21 days as treatment for non-severe respiratory exacerbations. Clinical data and a parent-proxy cough-specific quality of life (PC-QOL) score will be obtained at baseline, at the start and resolution of exacerbations, and on day 21. In most children, blood and deep-nasal swabs will also be collected at the same time points. The primary outcome is the proportion of children whose exacerbations have resolved at day 21. The main secondary outcome is the PC-QOL score. Other outcomes are: time to next exacerbation; requirement for hospitalization; duration of exacerbation, and spirometry data. Descriptive viral and bacteriological data from nasal samples and blood inflammatory markers will be reported where available.

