#### Parent-proxy cough-specific quality of life score

The parent-proxy cough-specific quality of life (PC-QOL) score is a 27-item questionnaire designed to assess the level of frequency of feelings (15 items) and worry (12 items) related to their child’s cough. It uses a seven-point Likert-type scale, with higher scores reflecting less frequency and fewer worry concerns (that is, greater QOL) [55,56]. The minimal important difference is 0.62 as determined by the distribution method, and 0.9 as determined by the anchor method [57].

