#### Statistical analysis for secondary outcomes and aims

For the clinical secondary outcome (secondary aim 1), the *t*-test or the Mann–Whitney test will be used for continuous variables (depending on normality of data distribution). A Kaplan-Meier curve will be constructed for each group for time to resolution and time to next exacerbation, as reported previously [67]. For secondary aim 2 (factors that predict response to antibiotics), univariate analyses will be used to examine several biologic factors (for example, smoking, age, ethnicity, underlying etiology, detection of virus (any versus none, then single versus multiple viruses), presence of azithromycin resistance, and levels of blood markers (IL-6, IL-10, IP-10)). Factors with *P*<0.2 will be included in a logistic regression model. Potential interactions (for example,. between viruses and bacteria) will be examined in the model. Descriptive data will be used for secondary aim 3 (point prevalence of respiratory pathogens).

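### PC-QOL, the main secondary outcome, is sized for non-inferiority (limit 0.9), but the stated t-test or Mann–Whitney test does not address that limit

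*Protocol article*

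**What the plan says.** **Design.** Under Sample size, the protocol article treats PC-QOL as a non-inferiority outcome: "Based on a non-inferiority limit of 0.9 (minimum important difference [57]) and standard deviation of 0.9". It claims 99.9% power at one-sided α = 0.05 with a one-sided 95% confidence interval, for 136 of the 170 enrolled children (80% retention).

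**Origin of the limit.** The section on the PC-QOL score gives two values: "The minimal important difference is 0.62 as determined by the distribution method, and 0.9 as determined by the anchor method". Sample size takes the second, does not mention the first and gives no reason. The defence of a wide margin in Sample size and in the Discussion concerns the 20% margin of the primary outcome, not this limit.

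**Analysis.** Under Statistical analysis for secondary outcomes and aims, a t-test or Mann–Whitney "test will be used for continuous variables (depending on normality of data distribution"). That section mentions no limit, no interval for the difference and no baseline value.

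**Data available.** According to the Methods paragraph of the abstract, the PC-QOL "score will be obtained at baseline, at the start and resolution of exacerbations, and on day 21". Secondary clinical outcomes names the score without a time point.

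**The concern.** The design section and the analysis section pose different questions. The design asks whether azithromycin is worse by less than 0.9 points. The tests ask whether the two arms differ at all. A reader of the results could be given a P value that does not answer the planned question, and the article does not say which reading governs when the two disagree.

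The normality check adds to this. A t-test comes with a confidence interval for the mean difference that can be set against 0.9. A Mann–Whitney P value cannot. Whether the planned inference is available would thus depend on the shape of the data.

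At stake are the interpretation of the main secondary outcome and, to a lesser degree, the precision that the earlier PC-QOL scores could add.

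**Working it through.** **Inputs.** Limit 0.9, SD 0.9, one-sided α = 0.05, 136 children analysed, so 68 per arm (170 × 0.80 = 136; 136 / 2 = 68), all from Sample size. Minimal important differences 0.62 and 0.9, from the PC-QOL section. Higher scores are better, so a deficit means a lower score on azithromycin. Normal approximation throughout.

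**1. The plan's own figure.**
- SE of the difference = 0.9 × √(2/68) = 0.154.
- Power at a true difference of zero = Φ(0.9/0.154 − 1.645) = 99.998%.
- The stated 99.9% is consistent with this and is not disputed.

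**2. Where the two procedures part.**
- Two-sided 5% t-test: significantly worse if the observed deficit exceeds 1.96 × 0.154 = 0.30.
- Limit of 0.9 with a one-sided 95% bound: non-inferior if the observed deficit is below 0.9 − 1.645 × 0.154 = 0.9 − 0.254 = 0.646.
- Observed deficits from about 0.30 to 0.646 satisfy both.

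**3. How often each verdict is reached, by true deficit d.** Significantly worse: Φ(d/SE − 1.96). Non-inferior: Φ((0.9 − d)/SE − 1.645). Every possible result meets at least one of the two conditions, so P(both) is the sum of the two less 1.

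| True deficit | Significantly worse | Non-inferior at 0.9 | Both |
|---|---|---|---|
| 0.30 | 49% | 98.8% | 48% |
| 0.45 | 83% | 90% | 73% |
| 0.62 | 98% | 56.7% | 55% |
| 0.90 | >99.9% | 5% | 5% |

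The first row also shows that a non-significant t-test is weak evidence of non-inferiority: with a real deficit of 0.3, the test misses it about half the time.

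**4. What the earlier scores could add.** Adjusting for a baseline score with correlation ρ multiplies the variance by 1 − ρ². The article gives no ρ, so these are assumptions.
- ρ = 0.3: factor 0.91, a 9% reduction.
- ρ = 0.5: factor 0.75, a 25% reduction. The one-sided half-width falls from 0.254 to 0.254 × √0.75 = 0.220.
- ρ = 0.7: factor 0.51, a 49% reduction. The half-width falls to 0.254 × √0.51 = 0.181.

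**5. Reading against 0.62 as well.** Power at a true difference of zero = Φ(0.62/SE − 1.645).
- SD 0.9: 99.1% (98.0% at one-sided 2.5%).
- Assumed SD 1.2: 91%.
- Assumed SD 1.5: 78%.

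**The case against.** **The comparison with the limit is planned.** Sample size names a one-sided 95% interval, and a t-based interval would deliver it. The analysis sentence is condensed, covers all continuous secondary variables, and interval detail is commonly left to an analysis plan that is not shown. Under a location-shift model, a Hodges–Lehmann interval could even be set against 0.9. This narrows the point but does not remove it: the article states a method for this outcome, and that method does not match its stated design.

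**The baseline scores may be used.** The article does not say whether raw or change scores are compared, and a t-test on change would use baseline. This stands. One can say only that no use is stated, and the gain is one of precision in a comparison that already has ample power at SD 0.9.

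**Stronger readings that a reader might infer, and that the documents do not support:**
- *The limit is wrong and must be 0.62.* The value 0.9 is the anchor-based minimal important difference, so it is not arbitrary. The value 0.62 is distribution-based, so the article gives no ground for saying that parents would notice a loss of that size. It is also itself a full minimal important difference (0.62/0.9 = 0.69 SD). What stands is that the choice is not explained.
- *Non-inferiority would be declared almost automatically.* That holds only near a true difference of zero. The chance is 56.7% at a true deficit of 0.62 and 5% at 0.9.
- *The score at resolution is uninformative because the child is at baseline by definition.* Intervention and follow-up defines resolution by cough, sputum colour and crackles. PC-QOL measures parental feelings and worry and is not part of that definition.

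**Conclusion.** The point holds as a mismatch between design and analysis for the main secondary outcome. The stated tests address zero difference, do not carry the limit of 0.9 forward, and are selected by a normality check under which one branch yields a P value that cannot be read against the limit at all.

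Under the article's own assumptions (68 per arm, SD 0.9), the two readings give opposite impressions for observed deficits of about 0.30 to 0.646. Being significantly worse and non-inferior at once is not a logical contradiction, but the article must say which reading governs. The lower end assumes a two-sided 5% test, since the article does not give the sidedness. A one-sided 5% test would move it to 0.254.

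The unexplained preference for 0.9 over 0.62 calls for a justification and a sensitivity reading, not a mandatory change of limit. The primary conclusion is not affected.

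**What to change.** 1. Name day-21 PC-QOL as the analysed score. It is already scheduled and matches the time point of the primary outcome.
2. Analyse it by ANCOVA with treatment, baseline PC-QOL (the enrolment score, with the exacerbation-start score added where available) and the stratification factors listed under Randomization.
3. Conclude non-inferiority if the one-sided 95% confidence bound for the adjusted mean difference (azithromycin minus amoxycillin-clavulanate) lies above −0.9, and state that this comparison governs.
4. Drop the normality-dependent choice of test. If residuals are skewed, use a bootstrap interval for the same adjusted difference.
5. Give the reason for 0.9 rather than 0.62, and report whether the bound also excludes −0.62 as a sensitivity reading.

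**Cost.** Wording and slightly more analysis work, with no new measurements. Children with a missing earlier score need a stated rule: the article assumes only 80% retention for this outcome, and Specimen collection notes that some children may be unable to attend when an exacerbation starts. The sensitivity reading at 0.62 has less power than the main comparison if the true SD is well above 0.9.

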### Specimen collection

At enrolment (baseline) all children will have a deep-nasal swab (NS) specimen collected. In a subset, additional specimens will be collected at baseline and during exacerbations, depending upon feasibility (some children may be unable to attend the study center at the onset of the exacerbation) and willingness of parents to allow additional NS collections and venepuncture procedures to be performed. These specimens are:

A deep NS specimen for respiratory viruses, respiratory bacterial pathogens (including antibiotic susceptibility testing), and other potentially important respiratory pathogens (*M. pneumoniae, Chlamydiales* spp) at baseline, and at the beginning and resolution of an exacerbation. The techniques used are identical to previous studies [49-51], in which the specimens were described as nasopharyngeal swabs. In this study, we have elected to call these specimens ‘deep-nasal swabs’ as it is anatomically accurate to do so. The NS specimens will be handled in accordance with our research laboratory protocol (see below).

Blood samples will be taken at baseline and at the beginning and end of each exacerbation for determination of C-reactive protein (CRP), interleukin (IL)-6 (a neutrophilic marker of inflammation [52]), serum amyloid A (SAA) [48], and markers of viral infection (IL-10, interferon γ-inducible protein (IP)-10) [53].

Sputum samples will also be taken at baseline and at the beginning and end of each exacerbation (when possible) for lower-airway microbiology cultures and antibiotic sensitivity tests.

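### The claim that 136 children suffice for eight predictors counts children, but the planned logistic model is limited by the roughly 27 expected non-resolved children, or 3.4 per factor

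*Protocol article*

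**What the plan says.** Secondary aim 2 (Aims of the study) looks for factors that predict response to the two antibiotics. The Sample size section states for this aim "we will be examining eight main factors" and concludes "thus a sample size of 136 exceeds the recommended minimum (n = 10 per factor". The 136 comes from the paragraph's preceding statement on PC-QOL, "for data from at least 136 children (assuming at least 80% retention of children enrolled", applied to the planned enrolment: "We plan to enroll 170 children (85 per arm".

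The eight factors listed there are smoking, age, underlying etiology, virus detection, azithromycin resistance, IL-6, IL-10 and IP-10. Virus detection is to be coded in two ways.

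The section Statistical analysis for secondary outcomes and aims gives the method: univariate analyses, after which "Factors with *P*<0.2 will be included in a logistic regression model", with interactions examined in that model. Its factor list is introduced as examples and adds ethnicity, which is not in the Sample size list.

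The Sample size section plans the primary outcome "with 20% non-inferiority margin to detect 80% resolution rate by day 21". Primary outcome defines resolution as a yes/no result for each child.

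**The concern.** Ten per factor is a rule of thumb for how many terms a regression can carry. With a continuous outcome, every child contributes fully and counting children is reasonable. With a yes/no outcome, the information about a coefficient scales with N × p × (1 − p), so the scarcer outcome limits the model. The protocol expects most children to resolve, so the scarce outcome is non-resolution, and the document gives no count of non-resolved children for this model.

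At stake is how far the predictor results can be trusted. Screening eight or more candidates on few non-resolved children risks unstable selection, odds ratios that are too large, and predictors that would not replicate. A reader told in advance that the sample exceeds the recommended minimum would give those results more weight than they can bear.

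**Working it through.** **Inputs**

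- Enrolled: 170. Retained: at least 80% (Sample size).
- Factors: 8 (Sample size), or 9 with ethnicity (Statistical analysis for secondary outcomes and aims).
- Rule: 10 per factor (Sample size).
- Planned resolution by day 21: 80%, so 20% non-resolved (Sample size).
- Model: logistic regression (Statistical analysis for secondary outcomes and aims).
- Assumptions: response in aim 2 means resolution by day 21, and the 80% rate applies to the children analysed.

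**The plan's own figure**

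170 × 0.80 = 136. The requirement is 8 × 10 = 80, and 136 > 80, or 136 / 8 = 17 children per factor. The statement reproduces, but only when children are counted.

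**The count that limits a logistic model**

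Smaller class = N × min(p, 1 − p), divided by the number of factors.

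| Resolution rate | Smaller class, N = 136 | Per factor (8) | Smaller class, N = 170 | Per factor (8) |
|---|---|---|---|---|
| 90% | 13.6 | 1.7 | 17 | 2.1 |
| **80% (planned)** | **27.2** | **3.4** | **34** | **4.25** |
| 70% | 40.8 | 5.1 | 51 | 6.4 |
| 60% | 54.4 | 6.8 | 68 | 8.5 |
| 50% | 68 | 8.5 | 85 | 10.6 |

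With 136 children the smaller class is at most 68, below the 80 needed, so no resolution rate meets the rule. With all 170 it is met only near 50% resolution (80 / 170 = 47% in the smaller class), far from the planned 80%.

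**What the rule would require, and what 136 children support**

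- Children analysed for 80 non-resolved: 80 / 0.20 = 400. At 80% retention that is 400 / 0.80 = 500 enrolled.
- Terms supported by 27.2 non-resolved: 27.2 / 10 = 2.7. That is two terms, or three at slightly under ten each (27.2 / 3 = 9.1).

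**More terms**

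With ethnicity as a ninth factor: 27.2 / 9 = 3.0. A tenth term, from the second virus coding or one interaction: 27.2 / 10 = 2.7.

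**Practical scale**

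Take one evenly split yes/no factor alone, with 136 children and 20% non-resolved. The information is 136 × (0.80 × 0.20) × (0.5 × 0.5) = 136 × 0.16 × 0.25 = 5.44. The standard error of the log odds ratio is about 1 / √5.44 = 0.43. The odds ratio detectable with 80% power at two-sided 5% is about exp(2.8 × 0.43) = 3.3, before adjustment for any other factor.

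**Missing specimens**

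Specimen collection says "In a subset, additional specimens will be collected at baseline and during exacerbations, depending upon feasibility". Blood belongs to these additional specimens, so the IL-6, IL-10 and IP-10 terms may rest on fewer than 136 children. The documents do not give the number.

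**The case against.** The strongest case for the plan has four parts.

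- **The arithmetic is right and the source is unseen.** 136 does exceed 80, and the reference cited for the rule is not at hand, so whether it counts subjects or events cannot be checked. This stands, but the point does not depend on that source. It depends on the protocol's own choice of a logistic model.
- **Ten per factor is only a rule of thumb, and the screen may leave a small final model.** Both are true, so overfitting is a risk and not a certainty. Screening does not rescue the justification, because every candidate is still tested against the same 27 or so non-resolved children.
- **Details belong in an analysis plan.** Much of the model specification does. The adequacy statement, however, is made in the article, and a later document cannot make it true.
- **The aim is secondary.** This stands. Enrolment, the primary non-inferiority comparison and the PC-QOL comparison do not rest on this sentence.

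A reader might also infer more than the documents support:

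- *That the laboratory factors rest on about half of the children.* The Abstract says blood and swabs will be obtained in most children, and Specimen collection gives every child a baseline nasal swab. Only the additional specimens come from a subset of unstated size.
- *That the model omits treatment or pools the arms.* The factors and interactions are introduced as examples in a condensed article, so neither list is closed. Aim 2 refers to both antibiotics, which is compatible with a treatment term or with separate models by arm.

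**Conclusion.** The concern holds in this form: the sentence on aim 2 applies the ten-per-factor rule to the wrong count. At the planned 80% resolution, 136 children give about 27 non-resolved, or 3.4 per factor for eight factors and 3.0 for nine. All 170 children would give 34, or 4.25 per factor. At the planned rate the shortfall against 80 is about threefold (80 / 27.2 = 2.9), and 136 children cannot meet the rule at any resolution rate.

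This rests on reading response as day-21 resolution and on taking the protocol's own rule at face value. It shows that the claimed adequacy is unsupported, not that the predictor results will be wrong. It should be corrected, but it does not touch the trial's main conclusion.

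**What to change.** 1. In Sample size, replace the comparison of 136 children with the expected number of non-resolved children, about 27 at 80% resolution (34 if all 170 contribute). State that by the same rule this supports two to three terms.
2. State that the outcome for aim 2 is resolution by day 21, if that is what is meant.
3. Reconcile the factor lists in Sample size and in Statistical analysis for secondary outcomes and aims, including ethnicity and the two virus codings.
4. Replace the P<0.2 univariate screen with one of two options: a pre-specified model of at most two to three terms, in which any interaction counts as a term; or a penalized (Firth or ridge) logistic regression of all listed factors. Penalization steadies the estimates but adds no information.
5. Report aim 2 as exploratory, and give the number of children and of non-resolved children behind each blood-marker estimate.

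The cost is a change of wording and a different regression routine, with no extra children or data. The downside is that fewer factors can be claimed as adequately tested.
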